# 8*.* STATISTICAL ANALYSIS

## 8.1 Methods

Analysis population

Three populations will be defined for the purposes of analysis.

Safety population

This comprises all patients randomised who had taken at least one unit of study medication.

Intent-to-treat (ITT) population

This comprises all patients in the safety population . The full analysis set arising from this population will comprise all available data from these patients, thus patients for whom there is no post-baseline data will not contribute to this data set.

Per-protocol (PP) population

This comprises all patients in the intent-to-treat population who did not deviate from the protocol in any way likely to seriously affect the primary outcome of the study.

The patients in each analysis population will be agreed on blind as to the treatment received and before statistical analysis begins.

The analysis of the primary efficacy variable will be performed on both the intent-to-treat and per-protocol populations.

The objective of the trial is to show the superiority of DHA versus placebo in preventing the occurrence of new vessels in patients with AMD.

STATISTICAL METHODS

All analyses will be carried out using SAS version 8.2 for PC. Tables and listings will be output directly for use in Word.

All data will be listed in individual patient listings.

Missing data will not be extrapolated.

Efficacy variables

The ocular criteria will concern systematically the study eye i.e. the eye not affected with CNV before entering the study.

The primary efficacy criterion is the time to occurrence of new vessels.

Secondary efficacy criteria:

- Percentage of patients for whom new vessels occur during the study,
- Change from baseline in visual acuity in LogMar units (ETDRS) and proportion of patients with a visual acuity decrease from baseline of more than 15 letters at ETDRS,
- Change from baseline in visual function (assessed with a multifocal ERG),
- occurrence and progression of drusen (number, size and area),
- DHA concentration increase in red blood cells membrane

Safety variables

The ocular criteria will concern both eyes.

- Slit Lamp Examination

- Profile of plasma lipoproteins

- Adverse or unexpected events

Other variables

Other variables recorded consist of demographic and baseline variables as well as history.

Concomitant medication, both systemic and ocular will be recorded.

Compliance to study drugs will be recorded as “yes” or “no” at each visit.

Extent of exposure will be calculated as the number of days on which the study medication has been taken.

Methods of analysis

Primary Efficacy Variable

The primary outcome of the study will be the time to occurrence of CNV in the study eye.

The occurrence rates in the 2 treatment groups will be compared using life-table methods.

The data will be analysed on an intent-to-treat principle so that data on time to occurrence of CNV is collected for all patients where possible, including early withdrawals from medication.

The difference between treatments will be tested using a log-rank test.

Prognostic factors which may affect the outcome, namely age, history of addiction to smoking, fish intake frequency, total cholesterol (TC) and APOE genotype will be considered for inclusion in the model.

Significance of these covariates, either time-dependent or time-independent, will be evaluated by proportional hazard model, the efficacy of the treatment will be adjusted by these covariates if necessary.

Data from patients withdrawn early will be considered censored at the point of withdrawal.

Secondary efficacy variables

The percentage of patients for whom CNV occur during the study will be compared between groups using a CHI square test or a Fisher test when required.

The change from baseline (time of enrollment ) in visual acuity scores at 6 months,Year 1, Year 2 and Year 3 will be compared between treatment groups by means of a Student t-test or a Wilcoxon Rank Sum test depending on data normality. The proportion of patients with a visual acuity decrease from baseline of more than 15 letters on ETDRS charts will be also compared across treatment groups using CHI square test or Fisher test.

The change from baseline in visual function (multifocal ERG),e.g change in amplitude and in timing, at Year 1, Year 2 and Year 3, will be compared between groups by means of a Student t-test or a Wilcoxon Rank sum test.

The progression of drusen (change from baseline in number, size and area) at 6 months, Year 1, Year 2 and year 3 will be compared between groups using a Wilcoxon Rank sum test .

The DHA concentration increase in red blood cells membrane at 6 months and at 3 years will be compared across groups using a Student t-test or a Wilcoxon test depending on data normality.

Safety variables

At each follow-up visit, the percentage of patients with changes (from the previous assessment) in the slit lamp examination will be compared between groups by means of a CHI square test or a Fisher test .

Change from baseline in profile of plasma lipoproteins will be compared between groups using a Student t-test or a Wilcoxon Rank Sum test depending on data normality.

Adverse or unexpected events will be counted and described by visit. In case of a sufficient number of adverse events, the percentage of patients having at least one adverse event will be compared between the 2 groups by means of a CHI square test. In case of serious adverse events, these will be counted and described completely and the corresponding patient profile will be detailed.

Other variables

The comparability of quantitative parameters between groups on D0 will be analysed by a Student t-test or a Wilcoxon Rank sum test depending on data normality. Qualitative parameters will be analysed by a CHI square test or a Fisher test depending on the number of patients in classes.

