The protective effect of DHA may be related to different mechanisms (15, 16). According to J. Seddon (8), the antithrombotic and hypolipidemic effects of the long chain omega3 fatty acids on the cardio-vascular system could also exert a beneficial effect on the vasculature of the choroids. Several other well known systemic effects of DHA could also play a preventive role in AMD, such as increased high density lipoproteins (HDL), decreased triglycerides (TG), increased apoE, anti-inflammatory role and protective effect on altered tissues such as in myocardium after ischemia reperfusion injury. This last effect, which may imply intracellular regulation as well as plasma membrane remodelling, is assumed to underlay the reduction in sudden death after myocardial infarction seen in large randomized control trials. Moreover, in the Gissi-Prevenzione trial (17, 18), omega 3 fatty acids supplied during 3.5 years reduced significantly (- 20%) overall mortality in myocardial infarction survivors, whom mostly correspond in age and sex to the population of subjects affected by age-related macular degeneration ( 55 years old). Finally a recent study comparing omega 6 and omega 3 supplementation in patients with carotid atherosclerosis has shown that indeed omega 3 incorporate into the arterial lesion and stabilize atherosclerotic plaques, in part by reducing its proliferative and inflammatory components (19). Therefore one might expect that once omega 3 fatty acids are incorporated into a human cell membrane they may exert their protective action locally.

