### 6.1.2 Examination schedule

The different visits will take place on D0, Month 6 (15 days), Year 1( 30 days),

Year 2 (30 days) and Year 3 ( 30 days).

Before inclusion, a baseline assessment will take place on D0. Besides validating the inclusion and exclusion criteria, this baseline visit will also enable the recording of demographic (including ethnicity) and baseline data. Data concerning some identified risk factors for AMD, as age and history of addiction to smocking, will be recorded. Moreover a diet questionnaire must be completed in order to assess the patient’s fish intake frequency.

Any general pathology (particularly diseases predisposing to bleeding or haemorrhage) and ocular pathology as well as any concomitant treatment will be recorded.

These data will be updated all along the study.

For patients previously supplemented with omega-3 fatty acids the corresponding stopping date will be recorded.

On each visit, ophthalmic assessments will include the following:

- Best corrected visual acuity measured with ETDRS charts
- Slit Lamp Examination
- Multifocal ERG (except on 6 month visit)
- Fundus photographs
- Fluorescein angiography (except on 6 month visit)

Moreover a complete profile of blood lipids will be performed on D0, at the 6 month visit and at the 3 year visit : fasting plasma lipoproteins [triglycerides (TG), total cholesterol (TC), HDL-C and LDL-C ] and fatty acids in serum and in red blood cell membranes (RBCM) will be measured. To this end 15 ml of venous blood will be collected after a 12 hour fasting period (as described in appendix I.D).

These data will allow first to evaluate for each patient the compliance to the treatment (DHA level in plasma) and the efficacy of DHA to penetrate the cell membrane (DHA level in RBCM), then to confirm the safety of the treatment concerning the metabolism of lipoproteins (fasting plasma lipoprotein profile).

Moreover since TC is considered as a risk factor for age-related macular degeneration, it will be considered for evaluation of treatment efficacy.

Furthermore, as previously mentioned (see section 4.2), apoE genotype of consenting patients will be evaluated on DNA of white blood cells, on D0.

10 ml of venous blood will be collected. The protocol for extraction of DNA from white blood cells and for evaluation of apoE allele is given in appendix I.E. If appropriate, the efficacy of the treatment will be assessed considering the apoE genotype .

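### The covariate rule for the adjusted treatment effect admits on-treatment cholesterol, factors chosen by significance and a consent-only genotype; the log-rank primary test itself is untouched

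*Protocol*

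**What the plan says.** Protocol section 8.1 (Methods of analysis, Primary Efficacy Variable) names the test of the primary endpoint: "The difference between treatments will be tested using a log-rank test". Section 8.2 sizes the trial on the same test.

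Section 8.1 then adds a modelling step. Five prognostic factors are candidates: "namely age, history of addiction to smoking, fish intake frequency, total cholesterol (TC) and APOE genotype will be considered for inclusion in the model". They are screened as follows: "Significance of these covariates, either time-dependent or time-independent, will be evaluated by proportional hazard model". The consequence is that "the efficacy of the treatment will be adjusted by these covariates if necessary". The section gives no significance threshold, no criterion for necessity and no fixed covariate set. It does not say which result governs if the log-rank test and the adjusted model disagree.

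Other sections bear on this:

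- Section 6.1.2, on when cholesterol is measured: "Moreover a complete profile of blood lipids will be performed on D0, at the 6 month visit and at the 3 year visit". The same section says total cholesterol will be taken into account when efficacy is evaluated, without limiting this to the D0 value.
- Section 2, on how DHA might work: "the antithrombotic and hypolipidemic effects of the long chain omega3 fatty acids on the cardio-vascular system could also exert a beneficial effect" on the choroidal vessels.
- Section 6.1.2, on genotype: "apoE genotype of consenting patients will be evaluated on DNA of white blood cells". The appendix list shows a separate consent form for the genetic study.
- Section 8.1, on gaps in the data: "Missing data will not be extrapolated".

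**The concern.** A treatment effect adjusted for a variable measured after randomisation no longer estimates the effect of being assigned to DHA if treatment changes that variable. Part of the effect is then assigned to the covariate. A covariate set picked by significance is not fixed before the data are seen. A factor that exists only for consenting patients shrinks the analysis set when it enters the model.

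At stake is the adjusted hazard ratio, which would probably be reported beside the log-rank p-value and read as the size of the benefit. If the two disagree, the protocol gives no rule for choosing between them.

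**Working it through.** **1. The plan's own figure.** Inputs from section 8.2: 3-year CNV risks of 30% and 15%, two-sided 0.05, 80% power, one year of uniform accrual, 20% drop-out, 1:1 allocation. Under exponential survival:

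- HR = ln(0.85)/ln(0.70) = 0.456.
- Hazards per year: 0.1189 (placebo), 0.0542 (DHA), loss 0.0744.
- Lachin-Foulkes: N = [1.96·√(4φ(λ̄)) + 0.84·√(2φ(λ₀)+2φ(λ₁))]² / (λ₀−λ₁)², with φ(λ) = λ² / P(event). This gives 244.2, rounded up to the stated 245.

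This reproduction lets early entrants be followed to year 4. With a fixed 3 years it gives 274, which is a separate matter. What counts here is that N is sized for the unadjusted log-rank test, so the covariate rule does not touch it.

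**2. Which factor can be time-dependent?** Smoking is a history item, genotype is fixed, fish intake comes from a questionnaire that the flow chart (6.3) shows at baseline only, and age advances equally for everyone. Only total cholesterol has scheduled later values, at month 6 and year 3. The year-3 value arrives at the end of follow-up, so in practice the month-6 value would enter. Scheduled angiography after D0 is at years 1, 2 and 3, so most detected events would carry that on-treatment value.

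**3. Effect on the adjusted hazard ratio.** The protocol gives no figure for DHA's effect on total cholesterol, so the inputs are assumptions: a fall of 0.2 to 0.5 SD, and a CNV hazard ratio of 1.2 to 1.5 per SD. If 0.456 is the total effect, the adjusted HR is 0.456 × (HR per SD)^shift:

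- 0.456 × 1.2^0.2 = 0.47
- 0.456 × 1.5^0.5 = 0.56

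Simulated Cox models (248 patients, 3 years, log-HR 0.4 per SD, shift from month 6) compare D0 cholesterol with time-dependent cholesterol:

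| Assumed truth | HR with D0 value | HR with time-dependent value |
|---|---|---|
| Direct HR 0.456, fall 0.5 SD | 0.39 | 0.46 |
| No direct effect, fall 0.5 SD | 0.85 | 1.00 |
| Direct HR 0.456, no change | 0.458 | 0.457 |
| No direct effect, rise 0.3 SD | 1.10 | 1.00 |

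The time-dependent model removes whatever passes through cholesterol. If DHA lowers cholesterol, that hides benefit; if DHA raises it, that hides harm.

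**4. Selection by significance.** Null treatment effect, five factors, screen at p<0.05 (an assumed threshold), 3,000 simulated trials per row. The Monte Carlo standard error is √(0.05×0.95/3000) = 0.4 points.

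| Covariate log-HR | Unadjusted | Selected model | Either may be claimed |
|---|---|---|---|
| 0 | 5.1% | 5.4% | 5.5% |
| 0.3 | 4.9% | 6.2% | 7.5% |
| 0.5 | 5.0% | 6.2% | 8.4% |

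A separate run of 1,500 trials with 20% drop-out gave 5.3%, 5.1% and 6.9%.

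**5. ApoE complete cases.** Expected events are 248 × (30%+15%)/2 = 55.8 before drop-out, or 55.8 × 0.8 = 44.6 if drop-outs contribute none. Power of a test in the genotyped patients only (Schoenfeld) is Φ(½√E·|ln 0.456| − 1.96). Consent rates are assumed:

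| Consent | Power from 55.8 events | Power from 44.6 events |
|---|---|---|
| 100% | 83.5% | 74.7% |
| 90% | 79.5% | 70.2% |
| 80% | 74.7% | 65.1% |
| 70% | 69.0% | 59.4% |

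Freedman's formula gives values about 4 points lower throughout. The starting level depends on the drop-out convention; the loss of about 15 points at 70% consent does not.

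**The case against.** The strongest reply is that the primary test is already fixed. Sections 8.1 and 8.2 both name the log-rank test, and nothing says the Cox step replaces it. This stands. A reader might infer that the primary test is biased or that the trial is underpowered because of the covariate rule. The documents do not support that, and the power losses above belong to an adjusted analysis that is not the named test.

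A reader might also infer a type I error of 7% or more. That needs a rule under which either result could be claimed, and the protocol states none. Selection alone gives 5.1% to 6.2%. The fair complaint is that nothing excludes the choice.

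On cholesterol, the introduction speaks of lipid lowering in general, but the lipid effects it goes on to list are higher HDL, lower triglycerides and higher apoE. A fall in total cholesterol is not named. Section 6.1.2 treats total cholesterol as a risk factor and the lipid profile as a safety check. So bias is possible, not established, and a fall in cholesterol would bias the result toward no effect, not toward a false claim of benefit. Section 6.1.2 also says baseline data will be updated through the study, which could conceivably cover smoking or diet; its scope is unclear, and the flow chart does not repeat the diet questionnaire.

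On apoE, declining to extrapolate missing data does not prescribe a complete-case Cox model, since a category for ungenotyped patients would be compatible. Section 6.1.2 makes the genotype assessment conditional on being appropriate. Handling of missing covariates can also be left to an SAP.

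Finally, the absence of baseline drusen from the list is a preference. Leaving out a prognostic factor does not invalidate a randomised comparison.

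What remains is not a gap for an SAP to fill. The protocol itself permits time-dependent covariates and ties adjustment to their significance.

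**Conclusion.** The point holds for the adjusted treatment effect and should be fixed; it is not critical. The log-rank test and N = 245 are unaffected.

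- **Cholesterol.** The adjusted hazard ratio could be biased toward no effect if DHA lowers total cholesterol: from 0.456 to 0.47–0.56 under the assumed inputs, and not at all if cholesterol does not respond. Permitted lipid-lowering drugs (section 5.5.1) are a further post-randomisation influence on the same variable.
- **Selection.** Type I error inflation is small: about 5 to 6% for the selected model. It reaches about 7% (5.5 to 8.4% across the assumed covariate strengths) only if either result could be claimed.
- **ApoE.** Patients are lost only if genotype enters a complete-case model and some decline. The number is unknown, because the protocol gives no consent rate.

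The structural part, that the rule allows a treatment-affected and data-picked adjustment, rests on the text alone. Every magnitude rests on assumptions.

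**What to change.** Revise the covariate paragraph of section 8.1:

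1. State that the unadjusted log-rank test in the ITT population alone decides the primary question, and that the per-protocol and adjusted analyses are supportive.
2. Remove the significance screen, the allowance for time-dependent covariates and the conditional adjustment. Replace them with one pre-specified supportive Cox model on D0 values only: treatment, age, smoking history, fish intake and D0 total cholesterol.
3. Keep apoE out of that model, and analyse it separately in genotyped patients with their number reported by arm.
4. Label any model with on-treatment cholesterol as exploratory.

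Adding D0 drusen area is optional; it is already measured. The cost is wording only, with no new data and no change in sample size. The change should be made before unblinding, because afterwards the choice of model cannot be shown to be independent of the results.

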## 8.2 Determination of sample size

The primary criterion is the time to occurrence of choroidal new vessels (CNV) in the study eye.

The occurrence rates of CNV in both treatment groups will be compared using a log-rank test.

According to previous studies (24) the 3 year risk of developing CNV in one eye is about 30 % (10% per year) for patients with CNV in the fellow eye.

Based upon expectation that DHA-treatment should reduce this rate to 15% at 3 years after D0 , sample size was thus performed assuming a 3 year CNV risk for the study eye in the treated group and in the placebo group to be 15% and 30% respectively.

The number of patients has been calculated with the Pass software for survival curves according to the following hypotheses:

- 2 tailed test
- Type I error  = 0.05
- Type II error  = 0.20 (80% power)
- Regular recruitment and Inclusion period: 1 year
- Follow up period per patient : 3 years
- Equal proportion of patients in each treatment group
- Drop-out rate in each group : 20%

Based on the above specifications the total number of patients should be 245.

Data on 248 evaluable patients are to be available (124 per group).

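### The secondary change-from-baseline endpoints are tested visit by visit without the D0 value as covariate, giving up some precision and leaving drop-outs' earlier visits out of the Year 3 test

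*Protocol*

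**What the plan says.** Section 8.1 (Methods, secondary efficacy variables) fixes these analyses:

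- **Visual acuity:** change at 6 months and Years 1, 2 and 3 "will be compared between treatment groups by means of a Student t-test or a Wilcoxon Rank Sum test depending on data normality".
- **Red-cell DHA:** "The DHA concentration increase in red blood cells membrane at 6 months and at 3 years will be compared across groups using a Student t-test"; the alternative is Wilcoxon, again according to normality.
- **Multifocal ERG:** change at Years 1, 2 and 3 by t-test or Wilcoxon, with no rule for choosing.
- **Drusen number, size and area:** Wilcoxon only, at 6 months and Years 1, 2 and 3.

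No covariate or longitudinal model is named for any of them. Covariates appear only in the proportional hazards model for time to CNV. The same section says "Missing data will not be extrapolated" and bases the full analysis set on available data. Sections 6.1.2, 6.1.3 and 6.3 show that the D0 value of all four endpoints is collected.

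**The concern.** The protocol itself chooses these methods, so this is not a detail left to an analysis plan. Three features deserve attention.

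- **Baseline.** A change score fixes the slope on baseline at 1. When the true slope differs, the change stays correlated with the D0 value. That adds variance, and a chance imbalance at D0 shows up in the particular result obtained. Section 8.1 examines D0 comparability but does not adjust the secondary endpoints for it.
- **Missing visits.** Each test uses only patients with a value at that visit. A patient who stops after Year 2 counts in the earlier tests, but those values do not inform the Year 3 comparison.
- **Choice of test.** For acuity and red-cell DHA the observed distribution decides between a comparison of means and one of ranks. The choice could differ between visits of one endpoint. For ERG it is open.

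At stake are the precision of the secondary results and their robustness to drop-out. Section 3 gives drusen progression particular weight among them.

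**Working it through.** **The plan's own figure.** The only sample size stated is for the primary log-rank test. Inputs from section 8.2: 3-year risks "in the treated group and in the placebo group to be 15% and 30% respectively"; accrual is given as "Regular recruitment and Inclusion period: 1 year", observation time as "Follow up period per patient : 3 years", allocation as "Equal proportion of patients in each treatment group" and attrition as "Drop-out rate in each group : 20" per cent; two-sided 0.05; 80% power. I used the Lachin-Foulkes formula with exponential event times, exponential drop-out of 20% over 3 years, 1 year of accrual and 4 years in total.

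- Hazards per year: placebo −ln(0.70)/3 = 0.1189; DHA −ln(0.85)/3 = 0.0542; mean 0.0865; drop-out −ln(0.80)/3 = 0.0744.
- Event probabilities: 0.3019 (placebo), 0.1525 (DHA), 0.2312 (at the mean hazard).
- N = [(1.960·√(4·0.0865²/0.2312) + 0.842·√(2·0.1189²/0.3019 + 2·0.0542²/0.1525)) / (0.1189 − 0.0542)]² = [(0.7054 + 0.3059)/0.0647]² = 244.2 with unrounded inputs, so 245.

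This matches the stated 245, and nothing below changes it.

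**Precision, equal SDs.** Let s be the common SD at baseline and follow-up, and rho their correlation within arm. The documents do not give rho, so the values are assumed.

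- Var(change) = 2(1 − rho)s²
- Var(ANCOVA residual) = (1 − rho²)s²
- Ratio = (1 + rho)/2

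| rho | Ratio | Variance saved | Extra patients the change score needs |
|---|---|---|---|
| 0.5 | 0.75 | 25% | 1/0.75 − 1 = 33% |
| 0.7 | 0.85 | 15% | 1/0.85 − 1 = 18% |
| 0.8 | 0.90 | 10% | 1/0.90 − 1 = 11% |

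A simulation with 99 patients per arm, sized for about 80% power on the change score, gave power of 0.79 for the t-test on change. ANCOVA gave 0.89, 0.85 and 0.83 at these three correlations.

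**Precision, unequal SDs.** Let k be follow-up SD divided by baseline SD (also assumed). In units of the baseline variance:

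- Var(change) = 1 + k² − 2·rho·k
- Var(ANCOVA residual) = (1 − rho²)k²
- Difference = (1 − rho·k)², which is never negative

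In large samples, therefore, ANCOVA cannot be less precise. Its advantage vanishes at k = 1/rho. At k = 1.5:

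| rho | ANCOVA | Change | Variance saved |
|---|---|---|---|
| 0.5 | 0.75 × 2.25 = 1.6875 | 3.25 − 1.5 = 1.75 | 3.6% |
| 0.7 | 0.51 × 2.25 = 1.1475 | 3.25 − 2.1 = 1.15 | 0.2% |
| 0.8 | 0.36 × 2.25 = 0.81 | 3.25 − 2.4 = 0.85 | 4.7% |

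**Missing visits.** At the planned drop-out, 0.20 × 248 = 49.6, so about 50 patients would have no Year 3 value and about 198 would enter the Year 3 test. This takes each drop-out as missing the Year 3 measurement.

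**The case against.** The best counter-argument is that the size is uncertain and may be negligible for acuity. Section 4.3.1 sets a minimum acuity for the study eye, which truncates the baseline distribution. Follow-up includes eyes that develop CNV, expected in 15% to 30%. A larger follow-up spread is therefore plausible, and the second table shows how little may then be gained. This stands: the equal-SD figures cannot be quoted alone.

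Other stronger readings are tempting but unsupported:

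- **The tests are invalid or biased.** Under randomisation with complete data they are valid; chance imbalance at D0 does not bias them on average. Bias arises only if drop-out is related to outcome.
- **Baseline is ignored.** It is subtracted; it is only not a covariate.
- **Drop-outs are discarded.** They count at every visit they attended, and section 9.1 continues assessments after protocol deviations. The 20% is a planning assumption.
- **Every test is picked on normality.** Among the efficacy endpoints that rule is stated only for acuity and red-cell DHA.
- **A 71% false-positive risk.** Counting acuity 4, ERG 2 × 3, drusen 3 × 4 and red-cell DHA 2 gives 24 tests, and 1 − 0.95^24 = 71%. This is not an error rate for the trial. The tests are repeated visits on the same eyes and overlapping measures of the same images, so they are not independent. Sections 2 and 4.2 already cite evidence that oral DHA raises cell-membrane levels, so those two tests are not credible nulls. Amplitude and timing are only examples of ERG measures. The superiority objective concerns new vessels alone.

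Naming a main visit for supportive endpoints is commonly left to an analysis plan. Its absence is no fault in itself, although it belongs in the new wording.

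**Conclusion.** The point holds as a matter of efficiency and missing-data handling for the secondary endpoints only. The specified tests can never beat baseline adjustment in large samples. The saving ranges from 25% of the variance (correlation 0.5, equal SDs) to almost nothing (0.2% at correlation 0.7, SD ratio 1.5). Correlation and SD ratio are both assumed, since the documents give neither. In addition, about 50 of 248 patients would contribute nothing to the Year 3 test at the planned drop-out. Choosing the test from the data is an avoidable weakness for acuity and red-cell DHA, and ERG needs a stated method. The change is worth making because the D0 data already exist. The log-rank analysis and the 245/248 patients stand.

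**What to change.** Replace the secondary-efficacy wording in section 8.1 as follows.

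- **Acuity and multifocal ERG:** one likelihood-based repeated-measures model per measure, with treatment, visit, treatment × visit and the D0 value. The Year 3 contrast is the main comparison. The model uses every observed visit without imputing, so it is compatible with the existing missing-data rule.
- **Red-cell DHA:** ANCOVA with the D0 value.
- **Drusen number, size and area:** rank ANCOVA with the D0 value, Year 3 as the main visit.
- **All four:** remove the normality-based choice of test, keep Wilcoxon as a sensitivity analysis, and report the other visits descriptively.

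The cost is revised wording and slightly more programming, with no new data, visits or patients. The repeated-measures model relies on data being missing at random, which should be stated. The ANCOVA analyses still use only patients with a value at the visit analysed, so for red-cell DHA and drusen the gain is in precision, not in recovery of drop-outs' earlier data.
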